### Sample size

We will use machine learning algorithms to predict the primary end point (i.e., the change in FM-UE 90 days after the stroke event compared to the initial FM-UE, see definition under “Outcomes”) as a function of the primary data set and the rehabilitation data set detailed in Tables 2, 3. Model development will start once 50 patients have been reached and continue throughout the study. To cope with the dimensionality of the problem, we will use lasso-regularized linear regression to select a sparse subset of the potentially correlated features. We will use a nested-cross validation setup to tune the regularization strength via the 1SE-rule [29] and obtain estimates of the fraction of the explained variance of the total variance in the primary end point on data not seen during model training. Due to the exploratory nature of the project and the complex models involved, a precise sample size calculation is not feasible.

**Table 2 Tab2:** Timeline for collecting the primary data set in the university hospital and other study sites

		Clinical data	Imaging data	Electrophysiological data	Laboratory data
0–24 h		NIHSS*			Blood sample*
25–48 h		mRS*	MRI* or CT*		
49–96 h		SAFE score		EEG	
				MEP	
		Grip strength			
		FMA			
		ARAT			
		BI*			
		Bells test			
		AST			
		BDI			
		SS-QOL scale			

Tests marked with * are part of the usual stroke work-up

Abbreviations: *NIHSS* National Institute of Health Stroke Scale, *mRS* modified Rankin Scale, *SAFE* Shoulder Abduction Finger Extension score, *FMA* Fugl-Meyer Assessment, *ARAT* Action Research Arm Test, *BI* Barthel Index, *MRI* magnetic resonance imaging, *CT* computed tomography, *Aphasie-Schnelltest, AST* aphasia quick test, *BDI* Beck’s Depression Inventory, *SS-QOL* Stroke-Specific Quality Of Life scale, *EEG* electroencephalography, *MEP* motor evoked potential

**Table 3 Tab3:** Overview over complete data collection

Location	Time point	Data set
University hospital of Tübingen, other recruiting study sites	Day 1–4 after stroke	Primary data set (see Table 1)
Rehabilitation hospital	On admission	Rehabilitation data set: FM-UE, BI and mRS
	Every 14 days during the stay and on discharge	• FM-UE, BI, mRS and questionnaire to capture soft influencing factors • Number, duration and type of neurorehabilitative treatments
University hospital	Day 90 after stroke	FM-UE, ARAT, BI, mRS, SS-QOL scale

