### Statistical methods

Statistical methods for primary and secondary outcomes.

Only those participants will a complete data set (including the 90 days follow-up examination or a lethal outcome) will be included in the statistical data analysis. Previous studies suggested that the FM-UE endpoints (i.e., the change in FM-UE 90 days after the stroke event compared to the initial FM-UE, see definition under “Outcome”) or the recovery trajectories of FM-UE scores can be clustered into 3 to 5 subgroups [4, 40]. We will first use time series clustering methods such as mixture of Gaussian processes [41] to identify such subgroups, then use the inferred cluster labels to build a classifier using lasso-regularized logistic regression to predict the group membership of the patient as a function of the primary data set and rehabilitation data set detailed in Tables 2, 3. The lasso regularization can automatically select a sparse subset of the significant features, reducing the dimensionality of the feature space and potentially the sample size required. We will use a nested-cross validation setup to tune the regularization strength via the 1SE-rule [29]. We can then use the Gaussian process model of the respective group to predict the primary endpoint and obtain estimates of the fraction of the explained variance of the total variance in the primary end point on data not seen during model training. If the linear model proves insufficient or unsatisfying, we will resort to non-linear regression models such as Generalized Additive Models (GAMs), which allow flexible nonlinear transformations of individual features of pairs of features [42]. Models for secondary endpoints will be built as well.

Interim analyses are not planned since this an observational study without interventions. No further analyses are planned apart from what is described under statistical methods for primary and secondary endpoints. Biobanking of blood samples will allow future (not yet planned) analyses of the relation of blood markers to stroke rehabilitation outcome.

Methods in analysis to handle protocol non-adherence and any statistical methods to handle missing data.

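### Statistical methods predicts the endpoint through presumed recovery groups and never compares this with the article's own direct lasso regression

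*Protocol article*

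**What the plan says.** The Protocol article describes two routes from the baseline and rehabilitation features to the primary endpoint, a continuous percentage of the initial FM-UE impairment recovered.

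**Statistical methods (through groups).** It opens with the suggestion from previous studies that "the recovery trajectories of FM-UE scores can be clustered into 3 to 5 subgroups" (the same is said of the endpoints), and on that basis commits to a sequence:
- Clustering: "We will first use time series clustering methods such as mixture of Gaussian processes [41] to identify such subgroups".
- Classification: the resulting labels become the target of a lasso logistic model on the features, which predicts each patient's group.
- Prediction: "We can then use the Gaussian process model of the respective group to predict the primary endpoint".

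Performance is judged by "estimates of the fraction of the explained variance of the total variance in the primary end point on data not seen during model training". A fallback follows: "If the linear model proves insufficient or unsatisfying, we will resort to non-linear regression models such as Generalized Additive Models (GAMs"). The section then says that nothing beyond the methods described there for the primary and secondary endpoints is planned.

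**Sample size (direct).** "We will use machine learning algorithms to predict the primary end point", and for this "we will use lasso-regularized linear regression to select a sparse subset of the potentially correlated features". Nested cross-validation and held-out explained variance are used here too. No groups appear.

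**The concern.** In Statistical methods the existence of groups is where the analysis starts; it is not put to the data. Apart from any early FM-UE values on which a group's Gaussian process may condition, the features reach the endpoint only through a choice among a few classes. No model without groups is named in that section as a competitor.

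Two things are at stake. First, explained variance is the study's own measure of success, and cutting a continuous outcome into a few classes before the features are used can lower it. A low figure could then be blamed on weak predictors when the grouping caused it. Second, the study wants to understand why some patients depart from the 70% recovery rule. Recovery types reported without a test against no types could answer that question with a product of the method.

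**Working it through.** **Figure to reproduce.** None. The article states no expected explained variance and no formal sample size calculation.

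**Inputs.**
- Number of groups K = 3, 4, 5: the range that Statistical methods cites from previous studies.
- True share of endpoint variance explained by the features, R² = 0.30, 0.50, 0.70: an assumption, because the article gives no value.
- One continuous, normally distributed endpoint with no real groups: an assumption, chosen to represent the case of concern.

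**Model.** Y = √R² · L + √(1 − R²) · e, where L (the best combination of features) and e are independent standard normal, with 1,000,000 draws. Y is cut into K groups by least-squares clustering, with group means c_k and boundaries b_k midway between neighbouring means. Given the features, the exact probability of group k is

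p_k(L) = Φ[(b_k − √R² · L)/√(1 − R²)] − Φ[(b_(k−1) − √R² · L)/√(1 − R²)].

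**Three predictions compared.**
- Direct: √R² · L, which attains the true R².
- One group per patient: the mean c_k of the most probable group.
- Probability-weighted: the sum over k of p_k(L) · c_k.

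Each is scored by 1 − mean[(Y − prediction)²]/Var(Y). Loss is the direct value minus the group value.

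| Direct R² | K | One group: R² | Loss | Weighted: R² | Loss |
|---|---|---|---|---|---|
| 0.30 | 3 | 0.169 | 0.131 | 0.288 | 0.012 |
| 0.30 | 4 | 0.211 | 0.089 | 0.296 | 0.004 |
| 0.30 | 5 | 0.231 | 0.069 | 0.298 | 0.002 |
| 0.50 | 3 | 0.369 | 0.131 | 0.476 | 0.024 |
| 0.50 | 4 | 0.415 | 0.085 | 0.490 | 0.010 |
| 0.50 | 5 | 0.437 | 0.063 | 0.495 | 0.005 |
| 0.70 | 3 | 0.556 | 0.144 | 0.660 | 0.040 |
| 0.70 | 4 | 0.610 | 0.090 | 0.682 | 0.018 |
| 0.70 | 5 | 0.638 | 0.062 | 0.691 | 0.009 |

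The loss runs from 0.062 to 0.144 with one group per patient and from 0.002 to 0.040 with weighting. Clustering and classification are ideal here.

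**Finite samples.** A second simulation estimated every step inside 5 outer folds, with 20 replicates per setting, assumed trajectories and features, and an ordinary Gaussian mixture of 3 to 5 groups in place of the Gaussian process mixture.

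| Data | n | Direct | One group | Weighted |
|---|---|---|---|---|
| No real groups | 200 | 0.485 | 0.169 | 0.356 |
| No real groups | 100 | 0.443 | 0.044 | 0.292 |
| Three real groups | 200 | 0.412 | 0.133 | 0.373 |
| Three real groups | 100 | 0.403 | 0.122 | 0.351 |

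The weighted loss without real groups is 0.485 − 0.356 = 0.129 and 0.443 − 0.292 = 0.151, well above the idealised 0.040. The one-group loss is large even when three groups are real (0.412 − 0.133 = 0.279 at n = 200), so much of it comes from the simulated pipeline and not from presuming groups. These results show that finite-sample loss may exceed the ideal figures, but they do not fix its size.

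**The case against.** A reader might infer that the plan predicts the endpoint only through groups and has no one-group model at all. The article does not support that. The Sample size regression is such a model, aimed at the same endpoint and scored on the same measure. The GAM fallback is also described as regression without mention of group labels, and it refers to a linear model although the only lasso model in Statistical methods is a logistic classifier.

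A reader might also infer that the clustering is forced to return 3 to 5 groups. That range is reported as a finding of previous studies. It is not set as the number to fit, and the rule for choosing the number may properly sit in a document not shown. In the finite-sample simulation, when 1 to 5 groups were allowed, BIC chose 3 or more in 0 of 40 data sets without groups, so an ordinary selection rule would not have invented them there.

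Nor is a large loss automatic. It nearly disappears with ideal probability weighting, and it would shrink if the group's Gaussian process conditions on the patient's own early scores, which the text leaves open. The framework is declared exploratory, and held-out scoring would expose a poor group route.

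All of this stands as a limit on the claim, but it does not remove it. The direct regression appears under Sample size, outside the section to which the planned analyses are confined, and is nowhere set against the group route. The GAM fallback addresses non-linearity, not the absence of groups. Held-out scoring of the group route alone can show that prediction is weak, but not whether the features or the grouping made it so.

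**Conclusion.** The point holds in limited form. Statistical methods routes endpoint prediction through a predicted group, starting from subgroups suggested by earlier studies, and does not compare this with the direct regression under Sample size. Its closing restriction, read literally, leaves that regression out.

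If recovery is continuous, the idealised loss of explained variance is about 0.06 to 0.14 when each patient is assigned to one group, which is the more natural reading of the text. It is about 0.04 or less when predictions are weighted by group probability. Both ranges assume a normal endpoint, ideal clustering and classification, 3 to 5 groups and a true R² of 0.30 to 0.70; none of these R² values comes from the article. A weighted loss of 0.13 to 0.15 should not be quoted as established, because it depends on one set of assumed trajectories and features.

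This is more than missing detail: the article specifies a pipeline, closes the list of analyses, and leaves out of that list the comparison that its own second model would supply.

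**What to change.** In Statistical methods:

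1. Name the direct lasso regression from Sample size as the one-group candidate, and bring it within the closing statement on planned analyses, so that the two sections agree.
2. Run it and the group route on the same outer cross-validation folds, with clustering, classification and tuning all repeated inside each training fold.
3. Choose between the routes by prediction error for the primary endpoint inside the training folds. Use groups for endpoint prediction only if they do better there; otherwise call them descriptive.
4. Report both held-out explained variances side by side, and say whether the group prediction uses one assigned group or group probabilities.

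The cost is a change of wording and slightly more analysis with a model the article already describes; no further data are needed. The downside is that the study may have to report that distinct recovery groups were not supported.

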### Data collection and management

#### Plans for assessment and collection of outcomes

Each participant will be assessed carefully within the first 96 h after stroke onset in the acute-care hospitals, using an extensive battery of standardized and validated clinical tests and scores. Additionally, laboratory, neuroimaging and electrophysiological data will be obtained. These data constitute the primary data set. In the rehabilitation hospitals some of the clinical scores of the primary data set will be obtained repeatedly at 14 days intervals, and the amount, type and intensity of neurorehabilitation treatment will be documented. These data constitute the neurorehabilitation data set. All data will be managed and integrated in a customized secure clinical data capture system (REDCap®, Research Electronic Data Capture) to which some of the data will be transferred automatically from primary clinical data information systems, while other data will be inserted manually.

All of the following clinical tests are conducted by or under the supervision of a qualified medical doctor of the University Hospital of Tübingen (Department of Neurology), a collaborating acute-care hospital of the Centre of Neurovascular Diseases, or a cooperating rehabilitation facility. Diagnostic neuroimaging is performed by a qualified medical doctor of the department of neuroradiology of the University Hospital of Tübingen or a trained medical doctor of the collaborating hospitals. All electrophysiological tests are performed by or under the supervision of a qualified medical doctor of the University Hospital of Tübingen, department of neurology, or of the collaborating hospitals.

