### Plans to promote participant retention and complete follow-up

The data will be collected on the stroke units of the collaborating acute-care hospitals (primary data set) and the rehabilitation hospitals (neurorehabilitation data set) in a clinical setting defined by current guidelines for stroke care and neurorehabilitation. It is, therefore, not expected that patients discontinue their participation in this study. Only the final examination 90 days after the stroke event will be performed, in most cases, outside of clinical treatment. It will take place in the University Hospital of Tübingen or in the rehabilitation hospital, if the participant is still in rehabilitative treatment. If a participant is unable to come to the University Hospital of Tübingen for the final examination, he will be visited at home by members of the study team.

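### FM-UE scores collected during rehabilitation are used as predictors, so the planned results cannot show how well the acute data predict recovery

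*Protocol article*

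**What the plan says.** The predictor set is fixed in two places in the protocol article. The Sample size section models the primary endpoint with lasso regression "as a function of the primary data set and the rehabilitation data set detailed in Tables 2, 3". The Statistical methods section builds a lasso logistic classifier to "predict the group membership of the patient as a function of the primary data set and rehabilitation data set detailed in Tables 2, 3".

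Table 3 shows what the rehabilitation data set holds. The admission row reads "Rehabilitation data set: FM-UE, BI and mRS". The row for every 14 days and discharge lists "FM-UE, BI, mRS and questionnaire to capture soft influencing factors", together with number, duration and type of treatments. The section on assessment and collection of outcomes describes the repeated clinical scores and the treatment records and then says "These data constitute the neurorehabilitation data set". The section on the neurorehabilitation data set gives the same FM-UE schedule.

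The labels to be predicted come from FM-UE endpoints or recovery trajectories: "We will first use time series clustering methods such as mixture of Gaussian processes". The Gaussian process of the assigned group then predicts the endpoint, in order to "obtain estimates of the fraction of the explained variance of the total variance in the primary end point on data not seen during model training".

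The Objectives section and the abstract are narrower. They name the data collected within 96 h and the rehabilitation treatments as predictors. Neither names FM-UE measured in rehabilitation.

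**The concern.** The analysis text gives the models more than the objective asks for, and the extra material is the outcome scale itself, measured later.

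Two separate consequences follow. First, a cluster label inferred from a patient's FM-UE trajectory is predicted from that same trajectory. High accuracy is then largely built in, and cross-validation does not remove it, because a held-out patient brings both the label and the scores that produced it. Second, the explained variance of the day-90 endpoint mixes two things: what the acute markers contribute, and what a patient's own FM-UE weeks later reveals.

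The Background sets the study against an acute-phase algorithm that classified 75% of cases correctly. A model that sees FM-UE during rehabilitation is not a like-for-like comparison. The Statistical methods section also says that nothing beyond the described analyses is planned, and no model restricted to the 96 h data is described. Followed as written, the plan yields no estimate of acute-phase prediction.

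**Working it through.** **Tracing the variables**

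| Item | Content | Source |
|---|---|---|
| Predictors | Primary plus rehabilitation data set | Sample size; Statistical methods |
| FM-UE in the rehabilitation set | Admission, every 14 days, discharge | Table 3 |
| Cluster labels | FM-UE endpoints or trajectories | Statistical methods |
| Endpoint | (day-90 FM-UE − initial FM-UE) / (66 − initial FM-UE) | Outcomes |
| Intended predictors | 96 h data; treatment type and amount | Objectives |

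The labels share inputs with their predictors. The endpoint does not: its formula uses only initial and day-90 scores, and Table 3 lists day 90 in its own row.

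**Timing.** The final examination can take place "or in the rehabilitation hospital, if the participant is still in rehabilitative treatment". On a 14-day schedule, such a patient's most recent score lies at most 14 days before day 90, and the discharge score cannot precede day 90. Assuming admission on day 10, scores fall on days 24, 38, 52, 66, 80 and 94. No cut-off before day 90 is stated. The article does not say how many patients this concerns.

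**Illustration of size.** The article states no R² to reproduce. Every input below except n = 200 and the endpoint formula is an assumption.

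- Recovery: FM(t) = FM₀ + r(66 − FM₀)(1 − e^(−t/τ)) / (1 − e^(−90/τ)) + error. FM₀ is uniform on 0–50, τ is 20 or 40 days and the error SD is 3. Scores are rounded and limited to 0–66.
- r has mean 0.6 and SD 0.3 before limits of −0.1 and 1. An assumed share of its variance (the acute signal) is carried by the 96 h data.
- Rehabilitation scores are on day 10 and every 14 days from day 24, with the last on day 24, 52 or 80.
- Ridge regression with 10-fold cross-validation; R² = 1 − Σ(y − ŷ)² / Σ(y − training mean)².

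| Assumed acute signal | R², 96 h data only | R², plus rehabilitation FM-UE |
|---|---|---|
| 0 | −0.01 | 0.66 to 0.86 |
| 0.2 | 0.16 to 0.17 | 0.68 to 0.87 |
| 0.4 | 0.34 to 0.35 | 0.69 to 0.86 |
| 0.6 | 0.51 to 0.52 | 0.73 to 0.87 |

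For labels, k-means with four clusters was applied to the initial, day 10, 24, 38, 52 and 90 scores (τ = 30), followed by multinomial logistic regression. Held-out accuracy from early data was 0.63, 0.67 and 0.72 for acute signals of 0, 0.2 and 0.4. With rehabilitation FM-UE added it was 0.94 in all three. The 0.63 without signal arises because initial FM-UE is one of the clustered values.

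A second simulation used other assumptions: error SD 2.5, admission on day 10, stay 14 to 100 days. R² for the ratio endpoint was 0.276 with acute data, 0.567 with admission FM-UE added and 0.732 with discharge FM-UE also added. On the day-90 FM-UE scale it rose from 0.479 to 0.899. Its stays reach day 10 + 100 = 110, so some discharge scores fall after the endpoint.

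**The case against.** **The article is condensed, and naming the whole data set may be shorthand for treatment variables.** This is possible, and an exact feature list is often left to a fuller document. But the article refers to Table 3 twice as the predictor source, defines the data set to include the repeated scores, excludes none of them, and rules out further analyses. That is a stated choice in conflict with the Objectives, not missing detail.

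**Predictors after 96 h are intended.** This stands. The primary objective is joint, so treatment type and amount belong in the model. The questionnaire items (support by relatives, motivation, self-training, therapist relationship) were collected deliberately as influencing factors and are not outcome measurements. The concern does not reach them.

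**The endpoint R² is not circular.** This also stands. A reader might infer that the rehabilitation scores define the endpoint. They do not, because it uses only initial and day-90 FM-UE. Predicting a later score from interim ones is legitimate updated prediction; it simply answers another question. Circularity applies to the labels.

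**Leakage through clustering is not established.** A reader might infer from the order of steps that clusters are fitted once on all patients, including those held out. The text does not say so. Its promise of performance on unseen data could mean refitting within folds, while nested cross-validation is described only for tuning. The passage is ambiguous.

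**The study is exploratory, and the simulations do not run the planned pipeline.** Both are true. They limit what can be said about size, but not the mismatch between predictors and objective.

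**Conclusion.** The point holds in this form: the stated predictor set includes FM-UE from rehabilitation, the label prediction is circular as a result, and the endpoint R² would not be evidence of acute-phase prediction. This follows from the text alone.

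The size does not. The simulations show only that the inflation can be large, even when the acute data carry no signal. A reader might infer that more than half of the reported R² would come from the patient's own later scores. That is not supported as a general statement. In the second simulation the share is (0.732 − 0.276) / 0.732 = 62% on the ratio scale, but (0.899 − 0.479) / 0.899 = 47% on the FM-UE scale. In the first, with acute signal 0.6, it runs from (0.73 − 0.52) / 0.73 = 29% to (0.87 − 0.52) / 0.87 = 40%. Nor was it tested whether the lasso would crowd out MEP, EEG, imaging or laboratory markers.

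The point still needs correcting before analysis, because the main result would otherwise leave the acute-phase part of the primary objective unanswered.

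**What to change.** In the Sample size and Statistical methods sections:

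1. List the predictors explicitly. Exclude FM-UE collected in rehabilitation from the main classifier and the main endpoint model, and use it only to define trajectories. Likewise exclude rehabilitation BI and mRS from the models for their own endpoints.
2. Report held-out explained variance for the 96 h data alone, then with treatment type and amount and the questionnaire co-factors added. Together these two steps serve the joint objective.
3. Label any model that uses interim FM-UE as updated prediction during rehabilitation, and admit only scores taken before day 90.
4. State that the clustering and the group Gaussian processes are refitted within each outer training fold.

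No new data are needed. The cost is plan wording, some extra computing for the refits, and a headline R² that will probably be lower.

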## Methods

### Objectives

The objective of the present study is to identify factors predicting motor outcome after stroke more accurately than hitherto possible, and rehabilitation treatments that are associated with improvement of arm−/hand function in individual motor stroke patients, using machine learning algorithms.

Primary objective: To determine which factors of the primary data set within 96 h of stroke onset and which type and amount of rehabilitation treatment predict the primary endpoint, i.e., the change in the FM-UE defined as 90 days FM-UE minus initial FM-UE, divided by initial FM-UE impairment.

Secondary objectives: Secondary endpoints are the quality of life, independence and range of activity of the UE measured by stroke-specific quality of life (SS-QOL) scale, modified Rankin Scale (mRS), Barthel-Index (BI) and Action Research Arm Test (ARAT) 90 days after the stroke event compared to the initial scores in the acute phase.

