### Recruitment

All acute stroke patients (> 2000 per year in the University Hospital of Tübingen and the 4 cooperating acute-care hospitals of the Center of Neurovascular Diseases) will be screened for recruitment, which is planned for a duration of 1.5 years. Up to 70% of all stroke patients present with UE paresis [2, 30], thus about 2000 patients (2000 patients /year × 1.5 years (recruitment period) × 0,7 (percentage of patients presenting with affection of UE)) are available for recruitment in theory. In practice (according to a preparatory analysis of our stroke unit data base over the preceding 2 years), approximately 60% of these patients will not have a sufficient deficit defined as FM-UE ≤ 50 initially or they will have a sufficient deficit, but it will not lasting beyond 96 h resulting in the patient not being in need of rehabilitation of the UE and not eligible for the project anymore (since he or she is not meeting the inclusion criteria anymore), or will die or be too frail for rehabilitation treatment, or will not fulfil the inclusion/exclusion criteria to begin with. Out of the remaining group of 800 patients there will be an expected further attrition by approximately 50% due to unwillingness to participate in the study or failure to obtain written informed consent, leaving approximately 400 patients for recruitment (i.e., a safety margin of 100 patients given the planned inclusion of 300 patients).

Unfortunately, the recruitment process showed that despite the conservative calculation we will probably only reach 200 patients.

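### The plan calls the features kept by a cross-validated lasso significant, but that selection has no significance level or false-selection control, and naming factors is the primary objective

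*Protocol article*

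**What the plan says.** All references are to the protocol article.

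- **Objectives.** The primary objective begins "To determine which factors of the primary data set within 96 h of stroke onset" and extends to the type and amount of rehabilitation treatment. The list of factors is therefore a primary result.
- **Sample size.** The plan uses "lasso-regularized linear regression to select a sparse subset of the potentially correlated features", so it concedes that candidates may be correlated. It also states that "a precise sample size calculation is not feasible".
- **Statistical methods.** Patients are first clustered by recovery trajectory. The plan will then "build a classifier using lasso-regularized logistic regression to predict the group membership". Of this step it says: "The lasso regularization can automatically select a sparse subset of the significant features".
- **Tuning and validation (both sections).** Nested cross-validation with the 1SE rule sets the penalty. The held-out data serve to estimate the explained share of the variance of the primary endpoint.
- **Recruitment.** On size, the article expects that "we will probably only reach 200 patients".
- **Trial design.** The framework is described as exploratory.

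**The concern.** *Significant* claims a property that the method does not have. The lasso keeps a feature when doing so helps prediction at the chosen penalty. No test is made, no error rate is fixed, and nothing limits the expected number of irrelevant features kept.

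The planned validation does not fill this gap. A model can predict well on unseen patients from a partly wrong list, because correlated features can replace one another with little loss of accuracy. Table 2 lists several measures of the same arm within 96 h (Fugl-Meyer, ARAT, SAFE, grip strength), alongside NIHSS, mRS, Barthel Index and motor evoked potentials. This is the situation in which selection among near-equivalents is unstable.

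At stake is what the trial may conclude about named acute markers and treatments. If kept features are presented as significant, later work on markers could follow factors that another sample of the same size would not return.

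**Working it through.** **The plan's own figure.** There is none to reproduce. The article gives no alpha, power, effect size or expected explained variance, and its recruitment arithmetic does not bear on selection error. The size was therefore examined by simulation.

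**Input from the article.** About 200 patients; lasso linear regression (Sample size) and lasso logistic classification into 3 to 5 groups (Statistical methods); 1SE rule.

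**Assumptions, not in the article.**
- Candidate features: 40, 60 or 80. About 60 can be counted from Table 2 and the data set descriptions.
- A block of 8 overlapping motor and severity measures with mutual correlation 0.6 to 0.9; all other correlations 0.1.
- 5 or 8 true predictors, of which 1 to 3 lie in the motor block.
- True R² from 0.3 to 0.6; n = 200 and also 150.
- 10-fold cross-validation. For the logistic model, groups were formed by cutting the simulated outcome into equal parts, not by trajectory clustering.

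**Definitions.**
- False share = kept features with zero coefficient in the generating model / all features kept.
- Motor stand-in = a false selection inside the motor block.
- Overlap of two lists A and B from independent samples = |A ∩ B| / |A ∪ B|.

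**Linear lasso, 1SE rule.** The grid has 2 × 3 × 3 × 3 × 2 = 108 settings (n, number of features, correlation, placement of true predictors, R²), with 12 repetitions each.
- Features kept: mean 7.5.
- False share: mean 35%, range 20% to 53%.
- Motor stand-ins as a share of the whole list: 5% to 35%.
- Overlap: mean 0.38, range 0.09 to 0.63.

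**Central linear case** (n = 200, 60 features, correlation 0.8, 5 true predictors, R² 0.5; 100 repetitions).
- Kept: 7.56. True factors found: 96%, so 5 × 0.96 = 4.8 true and 7.56 − 4.8 ≈ 2.8 false per list.
- False share, averaged over repetitions: 34%.
- Motor stand-ins: 19% of the list and 40% of the motor tests kept.
- Overlap: 0.52.

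**Logistic lasso, 1SE rule** (n = 200, 60 features, correlation 0.8 or 0.9, R² 0.3 or 0.5; only 8 to 10 repetitions per setting, so rough).
- False share: 44% to 67% with 4 groups, 37% with 3 groups.
- Motor stand-ins: 13% to 21% of the list and 39% to 70% of the motor tests kept.
- Overlap: 0.24 to 0.36.

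**Selection frequency as an alternative.** In the central linear case, the first q = 8 features to enter the lasso were recorded on each of 50 half-samples (40 repetitions). A feature was named if its frequency reached a threshold π. The usual bound on expected false selections is q² / ((2π − 1) × number of features).

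| Rule | Kept | False share | True factors found | Bound on expected false selections |
|---|---|---|---|---|
| Single 1SE fit | 7.56 | 34% | 96% | none |
| π = 0.75 | 3.98 | 7% | 73% | 64 / (0.5 × 60) = 2.13 |
| π = 0.90 | 2.68 | almost none | 53% | 64 / (0.8 × 60) = 1.33 |

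**The case against.** The strongest reply is that this is one loose word in an exploratory study. The sentence says what the lasso *can* do and goes on to speak of reducing dimension. The Sample size section describes the same kind of selection without the word. The stated performance measure, explained variance on unseen data, suits the aim of predicting better than before. A correlated stand-in does predict the outcome; it is false only relative to a sparse generating model. The 1SE rule is also the more cautious choice: at the penalty that minimises cross-validation error, the false share in the central linear case was 66% instead of 34%. Resampling details could properly sit in an analysis plan that is not shown.

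Much of this stands, and it limits the point. A reader might infer any of the following, none of which the article supports:
- **That the list comes from a single fit and must be read as a set of test results.** Nested cross-validation refits the model, and the article gives no rule for deriving or reading the final list.
- **That dropped markers will be declared irrelevant.** Nothing in the article says so.
- **That about half the list would be stand-ins for correlated motor tests.** Motor stand-ins were 19% of the list in the central linear case and 13% to 21% in the logistic cases. Shares near half describe all false selections in some settings, or the false part of the motor tests kept.
- **That a second sample would return a largely different list.** This fits the logistic results but not the central linear case.

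What does not stand is that the exploratory label makes the word right. The label lowers the stakes, but the primary objective is still to name factors. The misstatement is in the text, so the point does not rest on a missing method.

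**Conclusion.** The point holds as a wrong property claimed for a primary result. The features kept are *selected*; the described procedure gives no ground for calling them significant, and its validation speaks to prediction only.

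The size depends on assumptions that the article can neither confirm nor refute. Roughly 20% to 53% of features kept by the linear lasso would be false, and 37% to 67% for the logistic lasso, where few repetitions and a narrower set of settings make the range less certain. These are ranges under assumed feature counts, correlations and R², not forecasts for this trial. The predictive part of the plan is not affected. The change should be made because it alters what may be concluded about named factors.

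**What to change.** 1. In Statistical methods, replace *significant* by *selected*, and state that selection carries no error rate.
2. Repeat the whole selection pipeline, including tuning, on resamples (for example 100 half-samples), and report the selection frequency of every candidate, kept or not.
3. Report strongly correlated tests, such as the arm measures, as groups.
4. State that non-selection is not evidence of irrelevance.
5. If a frequency threshold is used to name a factor, set it in advance and state its cost. In the illustration above, 0.75 cut the false share from about 34% to about 7%, but found 73% rather than 96% of the true factors. In an exploratory study that loss is a real trade-off, so full reporting of frequencies matters more than any cut-off. The illustration used a fixed number of features per half-sample, so its figures would not carry over exactly to the full pipeline.

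No further patients or data are needed. The cost is computing time and more cautious claims about named factors.
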